### Sample size {14}

The primary endpoint of this study is the number of unmet needs. Recent literature points out that PwDs have on average 1.87 unmet needs with a standard deviation of 2.0 [47]. The sample size calculation was based on an assumed reduction of the number of unmet needs of 35% and a randomization ratio of 1:2 (1: intervention group, 2: waiting list). In a previous study, where dementia care management was also carried out, and patients were recruited from GP practices, there was an intra-cluster correlation (ICC) of 0.16 with a variance of ICC of 0.06 and a cluster size of five (five patients per GP practice). This ICC, variance of ICC, and cluster size were also used to calculate the sample size for this study. Therefore, a sample size of *n* = 345 PwD and 69 clusters would be needed to demonstrate an implicit effect of 1.22 unmet needs in the intervention group compared to 1.87 unmet needs in the control group at a significance level of *α* = 0.05 and statistical power of 80%. A loss to follow-up of about 30% was assumed due to the elderly population and the inclusion of a waiting-list group. Overall, this requires the recruitment of *n*=465 participants of 93 clusters to demonstrate a significant intervention effect. Therefore, a total of *n* = 310 patients in the waiting-control group (recruited from 62 GP practices) and *n* = 155 patients in the intervention group (from 31 GP practices) will be necessary to detect a significant difference between the intervention and the waiting control group concerning a 35% reduction of unmet care needs.

The randomization ratio of 1:2 was used due to the higher probability of dropouts in the waiting control group, which is predominantly a problem in times of the COVID-19 pandemic and the introduced lockdowns, contact restriction and the high risk of severe COVID-19 progressions, subsequent hospitalization, and death in the elderly population.

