## Statistical methods

### Statistical methods for primary and secondary outcomes {20a}

All statistical analyses will be conducted using pseudonymized data. Initially, primary and secondary outcomes will be analyzed with descriptive analyses. At baseline, the randomization procedure will be verified by comparison of the intervention- and waiting-control group based on descriptive statistics for various variables (randomization check). Should significant differences between the intervention and waiting-control group be identified, analyses will be adjusted for relevant variables. Quantitative parameters will be evaluated using hierarchical multi-level analyses to consider the study design with cluster randomization using physician’s practice and physician’s networks as context variables.

Response rates will be calculated for each group at each time point of analysis and compared between groups. Due to the expression (data count variable) of the primary outcome (unmet needs), a (multi-level) Poisson regression model based on the intention-to-treat principle will be fitted.

Respective to the secondary outcomes, analyses will apply linear or logistic regressions. Concerning the within-trial cost-effectiveness analysis, the incremental cost-effectiveness ratio (ICER) will be calculated by application of the incremental cost per QALY (Quality-adjusted life years) gained by the intervention compared with the waiting-control group. Descriptive statistics will be used to demonstrate unadjusted incremental cost and QALY. Nonparametric bootstrap resampling will be used to handle sampling uncertainty in the ICER. The probability of cost-effectiveness will be calculated by the application of different willingness-to-pay (WTP) margins based on the net monetary benefit approach [53]. All analyses will be performed with the statistical software IBM SPSS Statistics (version 26.0.0.0. or later, IBM Corp., NY, USA) and STATA (version 16 or later, StataCorp. LLC, TX, USA).

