### Methods for additional analyses (e.g., subgroup analyses) {20b}

In addition to the intention-to-treat analyses, we will perform subgroup analyses with participants who received the intervention (per-protocol analyses). Further analyses will be performed with specific subgroups of the study sample (e.g., severity of dementia, different home care situations).

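### The planned Poisson model omits extra-Poisson variation implied by the sample size figures: little effect on the primary arm test, but about 13% to 15% false positives if subgroups are tested as subgroup-by-arm interactions

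*Protocol article*

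**What the plan says.** Under Statistical methods for primary and secondary outcomes {20a}, the protocol article reasons that unmet needs are a count and concludes that "a (multi-level) Poisson regression model based on the intention-to-treat principle will be fitted". The same section makes practice and physician network the levels of a hierarchical analysis. It names no dispersion parameter, robust variance or alternative count model.

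Under Sample size {14}, the planning figures are that "PwDs have on average 1.87 unmet needs with a standard deviation of 2.0", with an "intra-cluster correlation (ICC) of 0.16 with a variance of ICC of 0.06 and a cluster size of five".

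Under Methods for additional analyses {20b}, "Further analyses will be performed with specific subgroups of the study sample". Severity of dementia and home care situation are given as examples. The form of the test (interaction, or a separate analysis in each subgroup) is not stated.

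**The concern.** Being a count is not enough to justify a Poisson model. The variance must also equal the mean once the random effects are accounted for. The protocol's own planning figures put it well above the mean, so a Poisson model with model-based standard errors claims more precision than the data would carry.

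Where this matters depends on the level of the contrast. Arm is assigned by practice, and the practice random intercept can take up the excess variation there. A contrast between patients of the same practice has no such protection. Dementia severity and home care situation are patient characteristics that will normally vary within a practice. What is at stake is therefore a spurious claim that the intervention works better in one kind of patient than in another.

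**Working it through.** **Inputs**, all from Sample size {14}: mean 1.87; SD 2.0; ICC 0.16; five patients per practice; 69 evaluable practices (93 recruited); allocation 1:2. Assumed: two-sided tests at 1.96; the ICC applies to the unmet-needs count; the planning SD holds at 6 months; subgroup membership varies within practices; standard errors are model-based.

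**The plan's own figures.** The target mean follows: 1.87 × (1 − 0.35) = 1.2155, or 1.22. For the evaluable sample, using SD 2.0 and no inflation for clustering:

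- smaller arm = (1.960 + 0.842)² × 2.0² × (1 + 1/2) / 0.65² = 7.85 × 4.0 × 1.5 / 0.4225 = 111.5, so 112
- 112 / 5 = 22.4, so 23 practices; 23 + 46 = 69 practices; 69 × 5 = 345

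This matches the stated 345 in 69 clusters. With the design effect 1 + 4 × 0.16 = 1.64 the total would be about 548. That is a separate question, not pursued here. What matters here is the variance used. Poisson variances would give 7.85 × (1.22 + 1.87/2) / 0.4225 = 40 in the smaller arm, about 120 in total before clustering. So the stated size is consistent with a variance of 4.0, not with a Poisson variance.

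**Dispersion.**

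- Total variance: 2.0² = 4.0; ratio to the mean 4.0 / 1.87 = 2.14
- Between practices: 0.16 × 4.0 = 0.64
- Within practices: 4.0 − 0.64 = 3.36; ratio to the mean 3.36 / 1.87 = 1.80, where Poisson assumes about 1

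Cross-check: if counts were Poisson within practices, the between-practice variance would have to be 4.00 − 1.87 = 2.13, an ICC of 2.13 / 4.00 = 0.53. The plan uses 0.16.

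**Effect on a within-practice contrast.** The true standard error is √1.80 = 1.34 times the model-based one. The reported one is therefore 1 / 1.34 = 0.75 of what it should be, about 25% too small. False-positive rate = 2 × [1 − Φ(1.96 / 1.34)] = 14.4%.

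**Simulation under no effect.** Log-normal practice effects with gamma-Poisson counts were matched to mean 1.87, SD 2.0 and the ICC. Each dataset was fitted with a random-intercept Poisson model and tested by Wald at 1.96, with 2,000 to 4,000 runs per setting. The network level was left out. At 30% loss, 465 × 0.7 = 325.5 patients remain, so 93 practices of 3 and of 4 bracket the expected completers.

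| Practices × patients | Subgroup-by-arm interaction | Arm effect (primary) | Arm effect inside one subgroup |
|---|---|---|---|
| 69 × 5, ICC 0.16 (two sets of runs) | 14.4%, 13.4% | 5.8%, 6.4% | 6.0%, 6.4% |
| 93 × 5, ICC 0.16 | 14.2% | 5.6% | 6.0% |
| 93 × 4, ICC 0.16 | 13.8% | 5.6% | 5.5% |
| 93 × 3, ICC 0.16 | 13.0% | 5.2% | 5.3% |
| 69 × 5, ICC 0.16, subgroup prevalence 30% | 15.0% | 5.8% | 5.8% |
| 69 × 5, ICC 0.05 | 15.2% | 5.7% | 5.6% |
| 69 × 5, ICC 0.30 | 10.2% | 6.9% | 6.2% |
| Control: counts Poisson within practices, 69 × 5 | 5.0% | 5.6% | 5.0% |

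Subgroup prevalence is 50% unless stated. The control row shows that the interaction excess comes from the dispersion. It also shows that an arm-effect rate slightly above 5% occurs even when the Poisson assumption is true. A further simulation with 93 uneven practices and about 325 completers gave 12.8% for the interaction and, for the arm effect, 6.4% unadjusted and 5.0% with baseline CANE in the model.

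**Remedies, interaction test.**

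- Mixed negative binomial: 3.8% at 69 × 5 (600 runs, about ±1.5 points) and 4.7% in the uneven-practice simulation. Its arm-effect rate at 69 × 5 was 5.0%.
- Poisson with practice-level robust standard errors: 6.6% and 6.0% at 69 × 5, rising to 7.6% with subgroup prevalence 30%.

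**The case against.** The strongest defence has four parts.

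- **The primary test is sound.** This stands. The rates at ICC 0.16 are 5.2% to 6.4%, and part of the small excess over 5% is present even with truly Poisson data.
- **No interaction test is specified.** This also stands, and it makes the 13% to 15% conditional. If each subgroup is analysed on its own, the arm comparison remains a between-practice one and stays near 5% to 6%. But an interaction is the standard way to compare effects between subgroups, so the condition is a realistic one.
- **An article leaves such detail to the SAP.** This stands in part. An SAP that is not at hand may add robust standard errors. The article does, however, name a specific model, and its own planning SD contradicts that model's variance assumption.
- **The SD is a literature value, unadjusted for covariates.** This is fair. Baseline adjustment would reduce the dispersion. At an assumed correlation of 0.5 with baseline it falls to 1.80 × 0.75 = 1.35, and the error rate to about 9%. But {20a} adjusts only when baseline differences prove significant.

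A reader might go further and take the brackets around the word multi-level to make the practice level optional, so that the primary test fails. A single-level Poisson test would indeed reject in about 29% of null trials (2.14 × 1.64 = 3.51; 2 × [1 − Φ(1.96 / √3.51)] = 29.5%). The documents do not support that reading. The Abstract commits the primary analysis to multilevel models, and {20a} puts quantitative parameters under a hierarchical analysis with practice and network as levels. The same sentence answers the inference that the linear and logistic models for secondary outcomes ignore clustering.

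**Conclusion.** The named count model conflicts with the plan's own dispersion figures, but the consequence is limited. Within-practice variance is about 1.8 times the Poisson value, so model-based standard errors for patient-level contrasts are about 25% too small. Subgroup-by-arm interaction tests would have about 13% to 15% false positives at the stated ICC, and 10.2% to 15.2% as the ICC moves from 0.30 to 0.05. The primary arm test, and arm tests within a subgroup, are nearly unaffected.

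This rests on the planning SD and ICC holding for unmet needs at 6 months, on subgroup variables that differ between patients of one practice, and on model-based standard errors. It does not show that the primary analysis is invalid or that clustering will be ignored.

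**What to change.** Add one sentence to {20a} saying that the model for unmet needs allows for extra-Poisson variation, and that this applies in particular to any subgroup-by-arm interaction under {20b}. Either of two forms would serve:

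- a mixed-effects negative binomial model with a practice random intercept, available in the Stata version already named; or
- the planned Poisson model with practice-level robust standard errors, which largely corrects the problem and keeps the chosen model.

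The negative binomial costs one extra parameter, and the robust option costs none. Stating the choice before the data are seen also avoids a change of model after overdispersion appears. The clustering levels need no change.

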**Methods:**

InDePendent is a two-arm, multi-center, cluster-randomized controlled intervention study. Inclusion criteria are age ≥70 years, cognitively impaired (DemTect ≤8) or formally diagnosed with dementia, and living in the own home. Patients will be recruited by general practitioners or specialists. Randomization is carried out at the physicians’ level in a ratio of 1:2 (intervention vs. waiting-control group). After study inclusion, all participants will receive a baseline assessment and a follow-up assessment after 6 months. Patients of the intervention group will receive advanced dementia care management for 6 months, carried out by specialized nurses, who will conduct certain tasks, usually carried out by primary care physicians. This includes a standardized assessment of the patients’ unmet needs, the generation and implementation of an individualized care plan to address the patients’ needs in close coordination with the GP. PwD in the waiting-control group will receive routine care for 6 months and subsequently become part of the intervention group. The primary outcome is the number of unmet needs after 6 months measured by the Camberwell Assessment of Need for the Elderly (CANE). The primary analysis after 6 months is carried out using multilevel models and will be based on the intention-to-treat principle. Secondary outcomes are quality of life, caregiver burden, acceptance, and cost-effectiveness. In total, *n*=465 participants are needed to assess significant differences in the number of unmet needs between the intervention and control groups.

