Secondary outcomes include (i) the Quality of Life in Alzheimer’s Disease (Qol-AD), a 13-item questionnaire designed to provide both a patient and a caregiver report of the quality of life. Each QoL-AD item is rated on a four-point scale, ranging from poor (1) to excellent (4). Results of the Qol-AD can be summarized in a score ranging from 13 to 52, in which higher numbers indicate higher quality of life [51]. (ii) Caregiver burden will be assessed by using the Zarit Burden Inventory, a caregiver self-report 22-item questionnaire. Each item on the interview is a statement which the caregiver is asked to rate using a 5-point scale. Response options range from 0 (never) to 4 (nearly always). The result of the instrument is a sum between 22 and 88, higher results indicate a higher subjective level of burden [43]. (iii) In addition to the quantitative analyses, we will perform qualitative interviews to assess the acceptance and satisfaction of the innovative care concept from different perspectives: people with dementia, caregivers, DCMs, and GPs. Qualitative data will be evaluated using content analyses [44]. (iv) Health economic analyses will assess the cost-effectiveness of the dementia care management compared to usual care by using the EQ-5D-5L [50], RUD (Resource Utilization in Dementia Questionnaire) [45], and FIMA (Questionnaire for Health-Related Resource Use in an Elderly Population) questionnaires [46]. The EQ-5D-5L is a standardized generic instrument for measuring health status. It has been widely used in population health surveys, clinical studies, and economic evaluation, measuring patients’ health utility in five dimensions: mobility, self-care, usual activities, pain/discomfort, and anxiety/depression. Health utilities will be combined with patients’ mortality as quality-adjusted life years by using the area under curve method. The RUD [45] and FIMA [46] instruments will be used to determine the utilization of informal care and caregivers’ productivity losses and the utilization of healthcare services from a payer’s perspective, respectively.

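### Incremental QALYs should be adjusted for baseline EQ-5D-5L utility whatever a significance test shows, because baseline utility carries half the QALY weight

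*Protocol article*

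**What the plan says.** The QALY is defined under Plans for assessment and collection of outcomes {18a}: "Health utilities will be combined with patients’ mortality as quality-adjusted life years by using the area under curve method". The Methods part of the abstract gives the timing: "all participants will receive a baseline assessment and a follow-up assessment after 6 months".

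Statistical methods for primary and secondary outcomes {20a} defines the ICER as incremental cost per QALY gained and continues: "Descriptive statistics will be used to demonstrate unadjusted incremental cost and QALY". The next sentence reads: "Nonparametric bootstrap resampling will be used to handle sampling uncertainty in the ICER". The probability of cost-effectiveness is then taken from net monetary benefit.

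Two general rules stand earlier in the same section. On covariates: "Should significant differences between the intervention and waiting-control group be identified, analyses will be adjusted for relevant variables". On clustering: "Quantitative parameters will be evaluated using hierarchical multi-level analyses to consider the study design with cluster randomization". Neither is tied explicitly to the economic analysis. No adjustment for baseline utility is named, and the unit that the bootstrap resamples is not given.

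**The concern.** Cost-effectiveness is a stated aim under Objectives {7} and a listed secondary outcome. With only two utility measurements, half the weight of a survivor's QALY is fixed before treatment starts. If increments are left unadjusted, or adjusted only when a baseline test happens to be significant, a utility imbalance of practical size but short of significance enters the numerator or denominator of every cost-per-QALY statement. Even without imbalance, the pre-treatment half adds variance that a covariate would remove.

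The imbalance need not be chance alone. Under {18a}, baseline is assessed by study nurses in the control arm and by dementia specialized nurses in the intervention arm. Under Implementation {16c}, a practice is allocated when its first patient consents, so later patients can be enrolled with the allocation known. Under {17a}, the trial is unblinded.

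**Working it through.** The article gives no numerical figure for the economic analysis, so there is nothing of its own to reproduce. The steps below use its design figures and marked assumptions.

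**1. QALY weights.** There are two time points and a horizon of 0.5 year. The trapezoid gives, for a survivor, QALY = 0.5 × (u0 + u6)/2 = 0.25·u0 + 0.25·u6. Baseline utility has weight 0.25 of 0.50, that is half. Patients who die have other weights, because mortality is combined with utility.

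**2. Effect of a baseline imbalance d.** The baseline term contributes 0.25d. If a fraction r of the imbalance is still present at month 6, the total is 0.25d(1 + r), at most 0.50d. For an assumed d = 0.03:
- r = 0: 0.0075 QALYs
- r = 0.5: 0.01125
- r = 0.7: 0.01275
- r = 1: 0.015

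The 0.25d from the baseline term equals what a true 6-month treatment effect of size d would produce.

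**3. What the significance rule lets through.** Inputs: 155 and 310 patients, five per practice (Sample size {14}); utility SD 0.25 and utility ICC 0.01 to 0.16 (assumed). SE of the baseline difference = 0.25 × √[DE × (1/155 + 1/310)], with DE = 1 + 4 × ICC.
- ICC 0.01: DE = 1.04, SE = 0.025
- ICC 0.16: DE = 1.64, SE = 0.031

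Multiplied by 1.96, the difference must exceed about 0.05 to 0.06 to be significant. Anything smaller stays unadjusted, worth up to about 0.012 to 0.015 QALYs from the baseline term, and up to twice that if it persists.

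**4. Precision.** Assume equal SD s at both times and correlation r within arm.
- Unadjusted variance = 0.0625·s²·(2 + 2r)
- Variance given baseline utility = 0.0625·s²·(1 − r²)
- Ratio = (1 − r)/2

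For r = 0.5, 0.6 and 0.7 the ratio is 0.25, 0.20 and 0.15. The adjusted SE is then 50%, 45% and 39% of the unadjusted SE. This sets aside deaths and any difference in clustering between the two analyses.

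**5. Resampling unit (conditional).** Only if single patients were resampled would the bootstrap SE be too small, by the factor √DE. Coverage of a nominal 95% interval is then 2Φ(1.96/√DE) − 1. With five per practice:

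| Assumed ICC | DE | True SE / bootstrap SE | Coverage |
|---|---|---|---|
| 0.01 | 1.04 | 1.02 | 94.5% |
| 0.05 | 1.20 | 1.10 | 92.6% |
| 0.10 | 1.40 | 1.18 | 90.2% |
| 0.16 | 1.64 | 1.28 | 87.4% |

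A simulation with 31 and 62 practices of five (600 replicates) at ICC 0.16 gave 84% coverage for patient-level and 94% for practice-level resampling. The 0.16 comes from the sample-size section ("there was an intra-cluster correlation (ICC) of 0.16"), where it supports the calculation for unmet needs. The ICC of costs and of QALYs is not given.

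**The case against.** The strongest reply is that the quoted sentence on unadjusted increments describes presentation. It fits the section's opening plan to start with descriptive analyses, and it does not say that the ICER rests on those figures. That stands. A reader might infer that the protocol commits to an unadjusted ICER, but the text does not go that far. The general rule would also bring in adjustment after a significant difference, so not every imbalance passes through.

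A second reply is that chance imbalance does not bias a randomised comparison. It is part of the sampling variation that a correct interval already carries. This also stands: for chance imbalance the loss is one of precision. What remains is that a significance test is a poor trigger for a covariate known in advance to form half the outcome's weight.

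A third reply concerns the bootstrap. A reader might infer that it ignores the practices. The documents do not support that: nonparametric does not mean patient-level, the section states a general intention to respect cluster randomisation, and an article may leave the resampling unit to the analysis plan. The 87% coverage figure also borrows an ICC meant for another outcome. This part is therefore a request for confirmation and no error.

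**Conclusion.** The point holds for baseline utility. The article names only unadjusted increments for the economic analysis, and its one adjustment rule depends on a significance test. That rule lets a material but non-significant utility imbalance pass into the ICER and gives up precision that data already collected would supply.

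The weights of one half each follow directly from the stated design, for survivors. The other sizes are conditional. The 0.012 to 0.015 QALYs rests on an assumed utility SD of 0.25 and ICC of 0.01 to 0.16. The SE reduction to 39% to 50% rests on an assumed correlation of 0.5 to 0.7.

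It is not shown that the ICER will be biased by chance, that it will be computed from unadjusted figures, or that the bootstrap breaks up practices. If patients were resampled, coverage would lie between about 94.5% (ICC 0.01) and 87% (ICC 0.16), and the documents do not say where in that range costs and QALYs fall.

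**What to change.** State in the protocol or analysis plan that:

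- incremental QALYs are estimated from a model with arm, network and baseline EQ-5D-5L utility, whatever a baseline test shows;
- incremental costs are adjusted for baseline costs where RUD and FIMA are taken at baseline;
- these adjusted increments feed the ICER and net monetary benefit, and the unadjusted figures are kept as description;
- as a clarification, the bootstrap resamples whole practices within arm and refits the adjusted model in each replicate.

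The cost is one or two sentences and a few lines of analysis code, with no new data. Intervals may narrow through adjustment. If patient-level resampling had been intended, they may widen through clustering.
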